### 2.13 Adverse events reporting

In this trial, an adverse event is defined as any medical occurrence that is unexpected and which could be reasonably suspected to be related to participation in the research study. The collection of adverse events starts after the participants’ study enrollment. It will stop with the end of their participation in the study, except in case of a serious adverse event (SAE). If the event occurs before any training session, it will be reported as non-related to the intervention. All adverse events are recorded by the study coordinator on an ongoing paper log and monitored by the physician until resolved. The physician will judge the intensity of the event and its relationship to study procedures. All adverse events that meet the SAE criteria will be reported to the local Research Ethics Board as an SAE. A SAE for this study is any major medical issue causally related to the study intervention, including hospitalization, life-threatening conditions, and severe or permanent disability.

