### 2.5 Participant timeline

First, a research team member performs the initial contact over the phone. During this call, the study structure is introduced, and a pre-screening of potential participants with no major physical or medical limitations to exercise is done. Interested individuals who meet these two main criteria are then assessed for eligibility. Immediately after the pre-screening call, the interested and eligible participants will receive the information and consent form (ICF). During a preliminary call, the ICF will be further explained in detail, and oral consent will be obtained. Following this, the participants will be screened for major physical limitations to exercises (PARQ +). After obtaining written consent, the cognitive (MMSE) screening will be performed with a research assistant. Individuals confirmed with no cognitive impairment will be considered enrolled. After the first visit, participants will have 1 week without any assessment or intervention training to collect accelerometer data at home under their usual conditions. They are also instructed to collect their biological samples during days when they do not have any research visits. After this is done, participants will return to continue the remaining assessments (see Table 1).

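### Expected events need not be recorded as adverse events, and serious harm caused by a study test cannot be classed as a serious adverse event

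*Protocol article*

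**What the plan says.** The rules stand in one paragraph, section 2.13 of the protocol article; section 2.5 fixes when a participant counts as enrolled.

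- **Adverse event:** "any medical occurrence that is unexpected and which could be reasonably suspected to be related to participation in the research study".
- **Window:** "The collection of adverse events starts after" enrolment. Section 2.5 sets that point at the cognitive screen: "Individuals confirmed with no cognitive impairment will be considered enrolled". The rest of the baseline testing follows.
- **Events before training:** "If the event occurs before any training session, it will be reported as non-related to the intervention".
- **Recording:** "All adverse events are recorded by the study coordinator on an ongoing paper log and monitored by the physician until resolved".
- **Causality:** "The physician will judge the intensity of the event and its relationship to study procedures".
- **Serious adverse event (SAE):** "A SAE for this study is any major medical issue causally related to the study intervention", with hospitalisation, life-threatening conditions and severe or permanent disability given as examples.
- **Ethics board:** "All adverse events that meet the SAE criteria will be reported to the local Research Ethics Board as an SAE". The section states no other report to the board.

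**The concern.** Expectedness and suspected cause normally decide how urgently an event is reported. Here they decide whether it is an adverse event at all. A foreseeable exercise injury is then not an adverse event, and relatedness has to be suspected before the physician is asked to judge it.

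The paragraph also ties relatedness to three different things: participation in the study (adverse event), study procedures (the physician's judgement) and the intervention (SAE). These do not fit together. The physician may conclude that a study test caused a hospitalisation, and the event still fails the SAE definition.

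Two things are at stake. One is oversight: participants are older adults with cardiovascular risk factors who undergo demanding tests, and serious harm from those tests has no stated route to the ethics board. The other is the completeness of the harms record of a trial that, according to its Discussion, is meant to inform future programmes.

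**Working it through.** No arithmetic decides this point. The check applies the section 2.13 rules in turn to each kind of event.

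**Timing.** Enrolment follows the cognitive screen (section 2.5). Randomisation follows the completed baseline assessment (section 2.8.3). The baseline test sessions (T0) after the first visit therefore lie inside the collection window, before any training and before any arm exists.

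**Procedures concerned.** The maximal cycle test (section 2.4.3.1) is scheduled at T0, 6 and 12 months (Table 2). Hypercapnic, hyperoxic and carbogen breathing takes place during MRI (section 2.4.2.1), which Table 2 schedules at T0 and 12 months. Hypercapnic breathing also belongs to the combined NIRS/TCD recording (section 2.4.2.2), and Table 2 shows TCD at all three time points.

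| Kind of event | Adverse event, logged? | SAE? | Board report stated? |
|---|---|---|---|
| Expected, non-serious, from training | No | No | No |
| Expected, serious, caused by the intervention | No | Fits the SAE sentence alone | Unclear: the report covers adverse events that meet the SAE criteria, and this is not an adverse event |
| Unexpected, serious, from a T0 test | Yes; followed until resolved | No: fixed as unrelated to the intervention | No |
| Expected, serious, from a T0 test | No | No | No |
| Unexpected, serious, from a test at 6 or 12 months | Yes | Only if the intervention is held to be the cause | Only in that case |
| Not suspected at first sight to be related | No | Not assessed | No |

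**What the table shows.** Rows 1, 4 and 6 need not be recorded at all. Rows 3 and 5 are recorded but lose SAE status, in row 5 unless the intervention is blamed. Row 2 cannot be resolved from the text.

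**Scale of exposure.** If all 159 planned participants took every scheduled maximal test, there would be 159 × 3 = 477 of them, 159 at T0. Dropouts would lower this figure, and people tested but not randomised would raise it. It counts tests, not harms; the document gives no event rate from which to estimate lost events.

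**Between arms.** Arms 1 and 2 share one exercise programme at 64–95% of maximum heart rate (sections 2.3.1 and 2.3.2). Arm 3 stays at 64% or below (section 2.3.3). If more complaints count as expected where exercise is more intense, the filter removes more events from Arms 1 and 2 than from Arm 3. It should act much the same in Arms 1 and 2.

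**The case against.** Several points on the other side stand.

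- A reader might infer that serious harm from baseline tests vanishes from the safety record. The text does not support this. Unexpected harm of that kind is related to participation and occurs after enrolment, so it is logged, followed and judged against study procedures. Only expected harm, or harm not suspected to be related, escapes the log.
- A reader might also infer that the rule on pre-training events biases the comparison of arms. It cannot, because those events precede randomisation. Calling them unrelated to training that has not begun is not wrong in itself; the trouble comes from the SAE definition that builds on it.
- Section 2.13 does not say that other events are withheld from the ethics board. Further reporting rules may stand in a full protocol that is not shown. The point is therefore limited to the report that the article states.
- Entry requires only reasonable suspicion, which is a low threshold, and the physician's later judgement is a genuine second step. The threshold still excludes events that are wrongly dismissed at the start.
- Safety is not among the stated objectives, outcomes or analyses, and the article does not define which events count as expected. Under-counting between arms is therefore plausible but unproven.

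These points narrow the concern. They do not remove it, because the two definitions are stated rules and not detail left out of a condensed article.

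**Conclusion.** The concern holds in a limited form. As written, expected events need not be recorded, and events not suspected of being related never come to the physician for judgement. Serious harm caused by a study test is logged if unexpected, but at T0 it cannot be an SAE, and at 6 and 12 months it can be one only if the intervention is held responsible. The three referents for relatedness contradict one another and must be reconciled.

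The number of events affected is unknown. The primary and secondary analyses are unaffected. Any distortion between arms would concern mainly the two exercise arms against the stretching control, after randomisation, and it cannot be quantified from the document.

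The conclusion assumes that section 2.13 is applied as worded and that no fuller document sets a wider definition.

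**What to change.** Amend section 2.13, and apply the following from now on:

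1. Record every untoward medical event from enrolment, whatever its expectedness or suspected cause.
2. Define seriousness by outcome alone.
3. Have the physician record relatedness twice, once to the intervention and once to study procedures.
4. Use expectedness and relatedness only to decide which events get expedited reporting.
5. Tabulate post-randomisation events by arm, and list pre-randomisation procedure events separately.

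If a fuller protocol already does this, it is enough to align the published definitions with it.

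The cost is a short amendment, a revised log and a real though modest increase in the coordinator's recording over a year of follow-up per participant. Enrolment began in October 2021 and Table 1 lists the trial as recruiting, so events left off the log before the amendment may not be recoverable. The report of harms should say so and give the date on which the definition changed.

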## 3 Discussion

This project is in line with a major priority of the Canadian Institute of Aging and the WHO; to “add health to years.” This project will go beyond correlative observations by comparing the impacts of a combined intervention to physical exercise training alone on cognitive and brain function, as well as on peripheral vascular function in seniors living with CVRF. The composition of the intervention groups and the rigorous randomization procedure will help minimize bias and isolate the effect of the combined training. This project brings together experts from cognitive neuroscience, cardiology, neuropsychology, physiology, brain imaging, and kinesiology.

It is expected that the results of this multidisciplinary effort will help develop optimal and applicable approaches to prevent CVRF-induced neurocognitive deterioration. This will have a real-world impact by informing future interventions (experimental or clinical) about the ideal composition of an effective exercise or combined program targeting the average older population at risk of cognitive decline. Moreover, the neuroimaging component will be able to document the neurovascular mechanisms through which the intervention could improve cognition by talking into account each participant’s individual profile (genetic profile, physiological markers of cardiovascular health, and psychological profile). Exploratory pathways that could also modulate the impact of the training arms on cognition are also considered, which include diet patterns, sleep quality, cognitive reserve, chronic stress, and mood.
